### Interim analyses {21b}

When half of the cases are completed in each group, unblinding and interim analysis will be conducted by an independent statistician. In the middle of the trial, that is, when half of the participants are enrolled, the test will be continued after unblinding under the condition that the interim analysis is consistent with the hypothesis. If it is inconsistent or even contrary, whether to continue the trial, terminate the trial, or expand the sample size will be decided by the expert committee.

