#### Objectives {7}

This trial aims to determine whether intravenous low-dose esketamine (0.25 mg/kg) reduces the incidence of hypoxemia (defined as SpO_2_ < 90% for > 10 s) by ≥ 15% compared to placebo during propofol-sedated gastroscopy in patients with moderate-to-high risk OSA (STOP-Bang score ≥ 3), using a one-sided *α* = 0.025.

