### Sample size {14}

All calculations were performed using PASS 15.0 (NCSS, LLC), with parameters verified by an independent statistician. The sample size calculation was based on detecting a clinically meaningful difference in the primary outcome of hypoxemia incidence (SpO_2_ < 90% for > 10 s) between study groups. From our pilot data, we anticipate a 50% incidence of hypoxemia in the control group receiving standard propofol sedation. We hypothesize that low-dose esketamine will achieve an absolute risk reduction of 15%, corresponding to a 35% hypoxemia incidence in the intervention group. Using a one-tailed *Z*-test for proportions (unpooled) with 80% power (*β* = 0.20) and a significance level of *α* = 0.025 (selected because esketamine’s established respiratory safety profile makes increased hypoxemia biologically implausible; detecting non-inferiority/superiority is the sole clinical priority.), we calculated a minimum requirement of 132 participants per group. To account for potential 10% attrition, we will enroll 147 participants per group (*N* = 294 total). This conservative approach ensures adequate power even if the actual control group incidence varies between 45 and 55% or if dropout rates reach 15%. The one-tailed design is appropriate given esketamine's established respiratory safety profile and the clinical irrelevance of detecting increased hypoxemia risk with this intervention.

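### The unblinded half-sample look makes automatic continuation depend on an undefined condition, so the risk of abandoning a true 15-point benefit ranges from negligible to large and is absent from the power statement

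*Protocol article*

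**What the plan says.** Interim analyses {21b} sets the look as follows: "When half of the cases are completed in each group, unblinding and interim analysis will be conducted by an independent statistician". It then states the condition for carrying on: "the test will be continued after unblinding under the condition that the interim analysis is consistent with the hypothesis". The alternative leaves the choice to a panel of experts: "If it is inconsistent or even contrary, whether to continue the trial, terminate the trial, or expand the sample size will be decided by the" (the sentence is cut here). Continuation is therefore automatic on one branch. On the other branch, termination is one of three options.

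The section gives no estimate, P value, boundary or conditional power, and it does not say which statement of the hypothesis it means. The protocol has more than one:

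- Objectives {7} aims at a reduction "by ≥ 15% compared to placebo during propofol-sedated gastroscopy".
- Sample size {14}: "We hypothesize that low-dose esketamine will achieve an absolute risk reduction of 15%, corresponding to a 35% hypoxemia incidence in the intervention group".
- Trial design {8} and Statistical methods {20a} speak of a reduction without any threshold.

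Sample size {14} describes a single-stage one-sided Z-test with 80% power. Its robustness claim, "This conservative approach ensures adequate power even if the actual control group incidence varies between 45 and 55" per cent (or if dropout reaches 15%), does not mention the interim look.

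**The concern.** The condition is applied after unblinding, by people who can see the result, and it decides whether termination comes onto the table. The only hypothesis stated with a number is a 15-point reduction. If that number were used as a hurdle for the observed interim difference, a drug with exactly the planned effect would miss it about half the time by chance.

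If the phrase means only that the data do not rule out the planned effect, a miss would be rare. The stated rule thus leaves open how likely it is that a useful treatment is abandoned at half enrolment on noise, and the power statement does not describe a trial that can end there. This is a concern about lost power. The type I error consequences of expanding the sample are a separate matter.

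**Working it through.** **Inputs.** Control 50%, esketamine 35%, one-sided α = 0.025, unpooled Z-test, 132 evaluable and 147 enrolled per group (Sample size {14}). Interim at half of each group ({21b}): 66 of 132, or 73 or 74 of 147.

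**The plan's own figure.** The variance term is V = 0.50×0.50 + 0.35×0.65 = 0.4775, and n = (z_α + z_0.80)² × V / 0.15².

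- One-sided 0.025: (1.960 + 0.842)² × 0.4775 / 0.0225 = 166.6, so 167 per group.
- One-sided 0.05: (1.645 + 0.842)² × 0.4775 / 0.0225 = 131.2, so 132 per group.

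The stated 132 therefore matches α = 0.05, not the stated 0.025 (132/0.9 = 146.7 does give 147). At one-sided 0.025, power without any interim is Φ(0.15/√(0.4775/n) − 1.96), which is 70.3% at 132 and 74.9% at 147. Simulation gives 70.7% and 74.7%, and these are the baselines below. The gap between them and 80% exists before any interim look.

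**Chance of being referred to the committee, true effect 15 points.** These are exact binomial probabilities.

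| Reading of the condition: referred if | 66 per group | 73 per group | 74 per group |
|---|---|---|---|
| 95% CI lies wholly below a 15-point reduction | 2.3% | 2.7% | 2.6% |
| No reduction, or wrong direction | 4.8% | 3.9% | 3.8% |
| Observed reduction below 15 points | 47.0% | 46.8% | 52.5% |
| Not significant at one-sided 0.025 | 56.6% | 53.5% | 52.5% |

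The third row follows from the sampling error. At 73 per group the standard error is √(0.4775/73) = 8.1 points around a mean of 15. The jump from 73 to 74 is discreteness: 0.15×73 = 10.95, so a difference of 11 events passes, while 0.15×74 = 11.1, so 12 are needed. With other true effects at 73 per group, the 15-point reading refers 24% of trials at 20 points (50% vs 30%) and 70% at 10 points (50% vs 40%).

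**Power at the final one-sided 0.025 test, by what follows referral.** These are simulations of at least 1,000,000 trials per setting.

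| Rule | 132 per group, interim at 66 | 147 per group, interim at 73 |
|---|---|---|
| Committee always continues | 70.7% | 74.7% |
| Terminated if no reduction or wrong direction | 70.2% | 74.2% |
| 15-point reading, half of referred trials terminated | 59.4% | 62.0% |
| 15-point reading, all referred trials terminated | 48.1% | 49.3% |
| Significance reading, all referred trials terminated | 40.4% | 43.8% |

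The largest loss on the 15-point reading is 70.7 − 48.1 = 22.6 or 74.7 − 49.3 = 25.4 points. It would be larger with the interim at 74 per group, where referral is more frequent. On the significance reading it is 30.3 or 30.9 points. On the confidence-interval reading it cannot exceed the 2–3% of trials referred. Of the trials that miss the 15-point hurdle, 48% (132 per group) to 54% (147 per group) would reach significance if simply run to the planned end.

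**A numeric alternative.** With N per group in total, h observed, m = N − h remaining and interim difference d, conditional power under the planned effect is approximately Φ[(h·d + 0.15m − 1.96√(N·V)) / √(m·V)]. For N = 147 and h = 73, setting this to 10% gives d = (16.42 − 11.10 − 7.62)/73 = −0.031. Stopping would thus be considered only when esketamine looks about 3 points worse. Under the planned effect this triggers in about 1.2% of trials, and power moves from 74.7% to 74.6% (loss under 0.1 point). At 132 per group the loss is about 0.1 point.

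**The case against.** A reader might infer that the protocol demands an observed 15-point reduction at the interim, so that an effective drug is stopped almost half the time. The documents do not support that, for three reasons.

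- {21b} gives no number and does not refer to {7} or {14}. The 15 points there are an aim and a planning assumption about the true effect, and {8} and {20a} state the hypothesis with no threshold. In ordinary usage, data agree with a 15-point effect when they are compatible with it, and that reading refers only 2–3% of trials.
- Missing the condition does not stop the trial. Two of the committee's three options keep it going, so the 49% and 44% powers are worst cases.
- The near-half figure belongs to a true effect of exactly 15 points. At 20 points it is 24%.

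All of this stands. One detail of wording cuts the other way: {21b} treats a contrary result as an extreme form of an inconsistent one. This weakens the purely directional reading, though it does not establish the 15-point one.

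It can also be said that numeric futility limits belong in an analysis plan or monitoring charter that is not shown, and that the DMC section {21a} gives interim review to an independent body. That would answer a complaint about missing detail. It does not answer this one: the protocol does state a continuation condition with termination attached, and as worded the condition supports readings that differ more than tenfold in how often a useful drug is put at risk.

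**Conclusion.** The point holds as a badly fixed rule whose effect on power cannot be determined from the text. It does not hold as proof that the trial will stop an effective drug half the time. For a true 50% vs 35% effect, referral to a possible termination ranges from about 2% to 57% across four plausible readings. The power loss runs from zero (committee always continues) to about 23–25 points on the 15-point reading (interim at 66 or 73 per group), or about 30 points on the significance reading, if every referred trial is terminated.

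The figures assume the planning rates, no expansion of the sample and the unpooled one-sided test at 0.025. Sample size {14} reflects none of this. Its fall from 80% to 74.7% (147 per group) or 70.7% (132 per group) comes from the sample size calculation and must not be attributed to the interim. The matter should be corrected, but its practical weight depends on how the committee would act.

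**What to change.** Before the interim data are unblinded, replace the continuation condition in {21b} with a numeric, non-binding futility guideline. For example: the DMC may consider stopping for futility only if conditional power under the planned 15-point effect is below 10%; an observed reduction below 15 points, or a non-significant interim result, is not by itself a reason to stop. The 10% cut-off is an illustration, and the documents do not fix one. If an analysis plan or charter already holds a numeric rule, {21b} should refer to it. The amendment should also say whether the expert committee in {21b} is the DMC of {21a}.

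State in {14} the power with the rule included, after the separate α and sample size discrepancy has been resolved.

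The cost is a wording amendment and one conditional-power calculation by the independent statistician, with no extra patients. The power loss is under 0.1 point at 147 per group and about 0.1 point at 132. The small downside is that the committee has less freedom to stop on weak but still promising results.

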### Composition of the data monitoring committee, its role and reporting structure {21a}

The independent data monitoring committee (DMC) comprises statisticians, clinical experts, and ethics representatives, unaffiliated with the sponsor and investigator team, will monitor progress and protocol adherence, review data safety and interim analyses, and report directly to the sponsor’s governance board or independent ethics committee (not the study team). Interim findings are masked to investigators unless critical safety concerns arise.

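### The interim rule ties the visible course of the trial to the direction of the unblinded result, which allows investigators to infer that direction and undermines the stated masking

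*Protocol article*

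**What the plan says.** Interim analyses {21b} sets one look: "When half of the cases are completed in each group, unblinding and interim analysis will be conducted by an independent statistician". It then gives two branches. If the result is favourable, "the test will be continued after unblinding under the condition that the interim analysis is consistent with the hypothesis". If it is inconsistent or contrary, "whether to continue the trial, terminate the trial, or expand the sample size will be decided by the expert committee". No threshold is given for *consistent*.

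The DMC section {21a} says that the DMC reviews interim analyses and will "report directly to the sponsor’s governance board or independent ethics committee (not the study team"). It adds: "Interim findings are masked to investigators unless critical safety concerns arise". Critical safety concerns are the only exception.

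The protocol does not say who sits on the expert committee, whether it is the DMC, or whether investigators learn that a referral took place. Study setting {9} confirms a single centre.

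**The concern.** Masking of interim results protects the second half of a trial from the expectations of the people running it. That protection fails if the team can work out the result from what happens next. Here the rule is public and branches on the direction of the efficacy result. Continuation without referral follows only a favourable interim; referral, termination and expansion follow only an unfavourable one.

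The second half leaves room for expectation to act. The eligibility section provides for a fixed anesthesia team. Propofol top-ups are discretionary within 10–50 mg {11a}. Airway management is triggered once SpO2 falls below 90% {11a}, whereas the primary endpoint needs more than 10 consecutive seconds below 90% {12}, so speed of response can decide whether an event counts. Clinician satisfaction is a visual analogue score. The Introduction lists transient hypertension, tachycardia and emergence phenomena as potential, typically mild effects of the study drug, so the arm may sometimes be guessed. The concern is leakage of information; it does not depend on the alpha level or power of the interim look.

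**Working it through.** **The text.** Setting the two sections side by side gives these observable courses:

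- *Expansion.* Possible only on the unfavourable branch. The team must be told to recruit beyond 294, so the branch is disclosed whether or not a referral was announced.
- *Termination.* Also only on the unfavourable branch, but little conduct remains to be biased.
- *Unchanged continuation.* Certain after a favourable interim, and one of three options after an unfavourable one. It is therefore informative but not conclusive.

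**Inputs for the size of the signal.** Sample size {14}: "we anticipate a 50% incidence of hypoxemia in the control group", and an "absolute risk reduction of 15%, corresponding to a 35% hypoxemia incidence in the intervention group". Planned enrolment is 147 per group, so half is 147/2 = 73.5; 73 is used. The protocol gives no figure for the leakage itself. Its sample-size figure of 132 per group does not reproduce at the stated one-sided 0.025 with a "one-tailed *Z*-test for proportions (unpooled) with 80% power": (0.5×0.5 + 0.35×0.65)(1.960 + 0.842)²/0.15² = 166.6, or 167; one-sided 0.05 gives 131.2, or 132. That is a separate matter and does not affect this point.

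**Probability of a consistent interim.** Let c1 and c0 be the probabilities of a *consistent* result under 50% v 35% and under 50% v 50%. Each is the exact sum of Bin(x_C; 73, p_C) × Bin(x_E; 73, p_E) over all outcomes that meet the reading. Because the term is undefined, three assumed readings are used; the third applies the unpooled Z > 1.96.

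**What each observer learns.** If the branch is known, the likelihood ratio is c1/c0. If only continuation is seen, and the committee continues unchanged with probability q after an unfavourable interim (assumed equal in both scenarios), it is [c1 + (1 − c1)q] / [c0 + (1 − c0)q].

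| Reading of *consistent* | c1 | c0 | Branch known | q = 1/3 | q = 0.5 | q = 0.8 |
|---|---|---|---|---|---|---|
| Any difference favouring esketamine | 0.961 | 0.467 | 2.1 | 1.5 | 1.3 | 1.1 |
| Observed reduction of at least 15 points | 0.532 | 0.041 | 13.0 | 1.9 | 1.5 | 1.1 |
| One-sided p < 0.025 | 0.465 | 0.028 | 16.4 | 1.8 | 1.4 | 1.1 |

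Worked example, second row, q = 1/3: (0.532 + 0.468/3) / (0.041 + 0.959/3) = 0.688/0.361 = 1.9.

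With 66 per arm (half of 132) the branch-known ratios are 2.0, 10.8 and 17.9; with 74 they are 2.1, 16.3 and 16.3.

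**What expansion discloses.** It reveals the unfavourable branch. If the committee's choice does not otherwise depend on the true effect, the ratio is (1 − c1)/(1 − c0): 0.039/0.533 = 0.07 for direction only, 0.468/0.959 = 0.49 for the 15-point reading, and 0.535/0.972 = 0.55 for p < 0.025. So a lenient reading makes expansion the telling signal, and a strict reading makes known non-referral the telling one.

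**The case against.** A reader might infer that continuing without a committee decision simply tells the investigators the result. The documents do not support that. The committee may also continue after an unfavourable interim, so continuation alone does not identify the branch. No section says that investigators learn of a referral. An independent statistician does the analysis and the DMC reports outside the study team. If the expert committee is the DMC, the two routes to continuation could look the same from outside. The ratios of 13 and 16 therefore apply only to someone who knows the branch; with q near 1 the signal vanishes. Even then, what leaks is an undefined label, not an estimate or a p-value. All of this stands. It does not remove the disclosure that comes with expansion.

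The harm can also be overstated. Knowing the aggregate direction reveals nobody's allocation. Patients, endoscopists, anesthesiologists and assessors remain blinded, with foil-wrapped syringes of identical volume {17a}. The primary outcome is an SpO2 threshold verified by an independent Endpoint Adjudication Committee {5d}, and the airway protocol has a stated trigger. Bias would need a leak, then a guess at the arm, then different behaviour. These safeguards limit the risk, though they do not remove the discretion described above. A contrary interim, with more hypoxemia on esketamine, might also fall under the safety exception in {21a}; a merely inconsistent one would not obviously do so.

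Committee membership and communication procedures may be set out in a fuller protocol or a charter. But the branching by direction is stated here, and defining *consistent* elsewhere would not remove it.

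**Conclusion.** The point holds in a limited form. The interim rule allows investigators to infer the direction of the unblinded result and so undermines the masking promised in {21a}. Expansion or termination discloses an unfavourable interim. Unchanged continuation is informative to a degree that the protocol leaves open: a likelihood ratio of about 2 to 16 if the branch is known, and about 1.1 to 1.9 if only continuation is seen and q lies between 0.8 and one third. These figures rest on 73 per arm, the planning rates, the three assumed readings of *consistent* and the assumed q. The bias in the second half cannot be computed from the protocol. The conclusion is that the two sections need reconciling, not that the trial's results would be biased.

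**What to change.** Before the interim result is acted on, replace the branching rule in {21b}:

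- Send every interim result, whatever its direction, to the independent DMC of {21a}.
- State whether the expert committee is that DMC.
- Have the DMC send the study team one uniform message to continue unless a pre-set criterion is met.
- Allow a change of sample size only under a pre-set rule, or drop the option.

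The DMC already exists, so the cost is modest, but this is more than rewording. A criterion has to be written, because the protocol contains none. The discretionary power to expand is restricted, and a separate expert committee would lose its role. Some information will still leak, since continuation under any published criterion shows that it was not met. Recruitment began on April 1, 2025, so the change needs IRB approval and a registry update under {11b} and {25}.

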## Statistical methods

### Statistical methods for primary and secondary outcomes {20a}

All analyses will be conducted using SPSS 23.0 (IBM Corp) by a statistician blinded to group allocation. The primary outcome will be analyzed using a one-sided *Z*-test at *α* = 0.025, while secondary outcomes will employ two-sided tests with *α* = 0.05.

Continuous variables will be assessed using the Kolmogorov–Smirnov test examining for normality. Normally distributed data will be presented as mean ± standard deviation (SD). Non-normal data will be presented as median or interquartile range (IQR). Categorical variables will be presented as counts and percentages.

For the primary outcome of hypoxemia incidence, we will employ a one-sided Z-test for proportions to evaluate the hypothesized reduction in the esketamine group, reporting absolute risk differences with 95% confidence intervals. Secondary outcomes will be analyzed using appropriate statistical tests based on variable characteristics: continuous normally distributed variables will be compared using independent *t*-tests, while non-normal continuous data will be assessed with Mann–Whitney *U* tests. Categorical outcomes will be analyzed using *χ*^2^ tests or Fisher’s exact tests as warranted by sample sizes. For time-to-event outcomes such as duration of hypoxemic episodes, we will utilize Kaplan–Meier survival analysis with log-rank tests. Longitudinal physiological measurements including mean arterial pressure and heart rate will be evaluated using repeated measures ANOVA, with post hoc Bonferroni corrections applied to account for multiple comparisons while maintaining the overall type I error rate at *α* = 0.05. All comparative analyses will be conducted by a blinded statistician using SPSS version 23.0, with two-sided tests (*α* = 0.05) employed for all secondary outcomes to conservatively assess potential group differences.

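### Open-ended sample-size expansion after an unblinded interim, followed by an unadjusted Z-test, leaves the one-sided 0.025 error rate uncontrolled

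*Protocol article*

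**What the plan says.** Interim analyses {21b} schedules one look: "When half of the cases are completed in each group", an independent statistician unblinds and compares the groups. The next sentence times the look at half enrolled. If the result is favourable, "the test will be continued after unblinding under the condition that the interim analysis is consistent with the hypothesis". If it is not, "whether to continue the trial, terminate the trial, or expand the sample size will be decided by the expert committee". The section gives no numerical meaning for a consistent or inconsistent result, no maximum sample size and no change to the final test.

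Statistical methods {20a} fixes the final test without reference to the interim: "The primary outcome will be analyzed using a one-sided *Z*-test at *α* = 0.025". It reports an absolute risk difference with a 95% confidence interval.

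The data monitoring committee section {21a} has an independent DMC review interim analyses and states: "Interim findings are masked to investigators unless critical safety concerns arise". It does not say whether the DMC is the expert committee of {21b}.

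**The concern.** Expansion is offered only after an unfavourable unblinded result. The size of the second stage therefore depends on the first-stage effect, and the usual Z statistic on the pooled data no longer has its standard null distribution. A weak start gets diluted by extra patients and has a second chance to cross 1.96, while a strong start is left alone. The confidence interval has the same problem.

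At stake is the one confirmatory claim of the trial. Its error rate would depend on a decision taken after seeing the data under no stated rule, so 0.025 could not be claimed. This goes beyond detail left to an analysis plan. The protocol itself gives the decision to committee discretion and itself fixes an unadjusted test, so a later document that repaired this would have to change both statements.

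**Working it through.** **Inputs from the protocol.** Sample size {14}: "we anticipate a 50% incidence of hypoxemia in the control group", a 15-point reduction to 35%, 132 per group, and 147 per group (294 in total) after 10% attrition. Statistical methods {20a}: one-sided 0.025, critical value 1.96. Interim analyses {21b}: look at half the sample, about 73 per group, information fraction 0.5.

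**Assumed.** The trigger on the interim statistic z1 and the multiple k applied to total N. The protocol gives neither, so ranges are shown.

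**The plan's own figure.** Unpooled n per group = [p1(1−p1) + p2(1−p2)](zα + zβ)²/d², with 0.25 + 0.2275 = 0.4775 and d = 0.15.
- One-sided 0.025: 0.4775 × (1.960 + 0.842)²/0.0225 = 166.6, so 167.
- One-sided 0.05: 0.4775 × (1.645 + 0.842)²/0.0225 = 131.2, so 132.

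The stated 132 matches 0.05, not 0.025. At 0.025 the power is 70.3% with 132 per group and 74.9% with 147. That is a separate matter, but lower power makes an unfavourable interim more likely.

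**Error rate under expansion.** With planned N = 1 and the look at 0.5, the naive final statistic after expansion to k is Z = (√0.5·z1 + √(k−0.5)·z2)/√k. Given z1, the null probability of rejecting is 1 − Φ[(1.96√k − √0.5·z1)/√(k−0.5)].

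Example at z1 = 0.5:
- k = 1: (1.960 − 0.354)/0.707 = 2.27, probability 0.0115.
- k = 2: (2.772 − 0.354)/1.225 = 1.97, probability 0.0242.

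Doubling roughly doubles the chance of a false positive from that point. With k = 2 the gain disappears at z1 ≈ 1.20. Above that value, expanding lowers the probability.

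Integrating over the null distribution of z1, for the trigger z1 < 1:
- Region z1 ≥ 1, left unchanged: 0.0202.
- Region z1 < 1: 0.0048 without expansion (total 0.0250), 0.0106 with k = 2 (total 0.0308), 0.0130 with k = 3 (total 0.0332).

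| Expand if | k = 1.5 | k = 2 | k = 3 |
|---|---|---|---|
| z1 < 0 | 0.0260 | 0.0270 | 0.0285 |
| z1 < 1 | 0.0287 | 0.0308 | 0.0332 |
| z1 < 1.96 | 0.0276 | 0.0288 | 0.0300 |
| Worst case, N capped at k | 0.0290 | 0.0311 | 0.0335 |

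The worst case takes the most harmful N up to the cap at each z1.

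**If the committee always terminates instead:** 0.0247 (z1 < 0), 0.0202 (z1 < 1), 0.0084 (z1 < 1.96).

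**Check on binomial data** (2,000,000 trials, both rates 50%, look at 73 of 147 per group, unpooled Z): 0.0271 with no expansion, which reflects discreteness and the variance form. It rises to 0.0287 (z1 < 0, k = 2) and 0.0329 (z1 < 1, k = 2).

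**How often each trigger would occur under the design effect.** SE = √(0.4775/73) = 0.0809, so expected z1 = 0.15/0.0809 = 1.85. Then P(z1 < 0) = 3%, P(z1 < 1) = 20%, P(z1 < 1.96) = 54%.

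**The case against.** The strongest reply is that the inflation is conditional and modest. The same sentence that allows expansion also allows unchanged continuation, which leaves 0.0250, and termination, which lowers it. Doubling adds 0.2 to 0.6 percentage points. All of that stands, and it limits the claim to an error rate that is not controlled and can exceed 0.025.

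A reader might go further in four ways that the protocol does not support.
- **That the missing stopping boundary inflates the error.** Two looks each tested at 1.96 would give 0.042, but {21b} describes no early claim of success. A favourable interim only means carrying on.
- **That the error could reach 0.062.** That limit needs a second stage that may also be shortened. The clause allows only continuing, stopping or enlarging.
- **That expansion at the 0.031 level is close to a coin flip.** The 54% belongs to z1 < 1.96, where doubling gives 0.0288. The trigger behind 0.0308 is z1 < 1, which occurs about 20% of the time under the design effect.
- **That unchanged continuation reveals a favourable trend.** The committee may also continue after an unfavourable result.

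The remaining inconsistencies are matters of clarity. The primary outcome is observed during a procedure limited to 15 minutes, so half enrolled and half completed nearly coincide. The expert committee is undefined and could be the DMC, whose members include clinical experts. Unblinding by an independent statistician can be reconciled with masking of the investigators.

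**Conclusion.** The point holds in limited form. As written, the plan permits a results-driven, uncapped expansion followed by an unadjusted one-sided test at 0.025 and an unadjusted 95% interval, so neither has its stated property. If expansion is used and N doubles, the error is about 0.027 (trigger z1 < 0) to 0.031 (z1 < 1), at worst 0.0311. If N may triple, it is at most about 0.0335. Always terminating would give 0.008 to 0.025. These figures rest on assumed triggers and multiples, a look at half the information and the normal approximation. With no ceiling on N in the protocol, they are illustrations and not bounds on what the text permits.

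**What to change.** Amend {21b} and {20a} before any interim result is seen, choosing one route.

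1. **Blinded re-estimation only.** Any change in N is based on the pooled event rate across both groups, and the final Z-test stays as it is.
2. **Unblinded expansion kept.** State a numerical trigger and a cap on N. Replace the final test with an inverse-normal combination of the two stages at one-sided 0.025, with weights fixed at the planned information split, and report a confidence interval derived from the same test. This holds 0.025 whatever expansion is chosen and needs no alpha for the look, as long as no early efficacy claim is added.

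Under either route, state that the DMC of {21a} is the deciding committee and that only the DMC and the independent statistician see results by arm. Give one timing: outcome data complete on 147 participants in total (half of 294).

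The cost is protocol and DMC charter wording. Under the first route the sponsor gives up ad hoc expansion on unblinded data. Under the second it accepts a slightly less efficient weighted test.
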